### **2.2 Secondary objects**

The secondary objective of this study will be to investigate differences between the telesurgery and local surgery groups in terms of complications and adverse events, early recovery quality, physical functioning, early oncological outcome, task load of the surgeon and medical team, and robotic or telesurgery system status or malfunction.

### **3. Trial design**

This will be a prospective, multicenter, single-blind, non-inferiority, exploratory, randomized controlled trial aimed at exploring the safety and reliability of telesurgery.

Participants will be randomized to either the telesurgery group or the local surgery group.

There are four study periods:

- (1) Screening Period;
- (2) Randomization Period;
- (3) Surgery Period;
- (4) Follow-up Period.

[figure not shown]

Figure 1. Schematic Flowchart of the Study Design.

### 3.1 Study Arms

In this randomized trial, all participants will be randomized to either arm A (telesurgery group) or arm B (local surgery group).

### 3.2 Sample Size

According to the requirements of the "Guideline for the Design of Clinical Trials of Medical Devices" (published by CFDA), the number of trial cases was inferred based on the non-inferiority sample size

calculation method, and the number of cases was calculated through joint discussion by clinical trial institutions, major researchers, and statistical analysts.

The formula is as follows:

$$n_T = n_C = \frac{(Z_{1-\alpha/2} + Z_{1-\beta})^2 [P_C(1-P_C) + P_T(1-P_T)]}{(|D| - \Delta)^2},$$

where  $\alpha = 0.025$  (one-sided),  $\beta = 0.2$  (80% confidence), and the non-inferiority margin  $\Delta = 10\%$ . Assuming that the surgical success rate of the experimental group and the control group is equal, the expected surgical success rate of the two groups is 98% (i.e.,  $P_T = P_C = 98\%$ ). As the ratio between the two groups is 1:1, 31 subjects are needed in each group. Considering that the dropout rate of subjects during the trial is about 10% or more, this study plans to enroll 68 subjects, with 34 in the experimental group and 34 in the control group. If the dropout rate exceeds the expected 10%, resulting in insufficient valid data, the number of patients enrolled can be appropriately increased, and the proposed increase in the number of patients enrolled should be filed with the Ethics Committee of Chinese PLA General Hospital.

Urologic surgery is divided into upper and lower urinary tract surgeries. In this clinical trial, representative surgical methods of partial

nephrectomy and prostatectomy are selected for surgery. In the end, partial nephrectomy and prostatectomy in this scheme is no less than 30%, and each clinical center ensures that subjects are operated on for both partial nephrectomy and prostatectomy surgery. This information will be summarized after the end of the trial. According to the non-inferiority test, when the lower limit of the 95% confidence interval of the difference in surgical success rate between the two groups is  $> -10\%$ , the non-inferiority hypothesis is established, which can be considered to meet the qualified requirements of this clinical trial.

### **3.3 Randomization**

This study will adopt a random number distribution system. The random grouping table of subjects will be generated by independent statisticians (who will not participate in the clinical trial) from random coding units. The ratio of the test group to the control group will be 1:1. The seed number for generating the random table is fixed, and the process of generating the random table can be repeated. The generated random table of subjects will be imported into the random system by the random system administrator. All random numbers will not be used twice. After the successful screening of subjects, the random responsible person of each center will log in to the system and enter the basic information of

subjects according to the system prompts, including the date of birth and the name abbreviation, etc. The system will generate a unique random number for each subject and randomly allocate subjects to the groups.

We used stratified randomization with random block sizes of four.

Stratification was identified by the surgery type (prostatectomy and partial nephrectomy) with the randomization conducted separately for each stratum.

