### **3.2 Randomization**

This study will adopt a random number distribution system. The random grouping table of subjects will be generated by independent statisticians (who will not participate in the clinical trial) from random coding units. The ratio of the test group to the control group will be 1:1. The seed number for generating the random table is fixed, and the process of generating the random table can be repeated. The generated random table of subjects will be imported into the random system by the random system administrator. All random numbers will not be used twice. After the successful screening of subjects, the random responsible person of each center will log in to the system and enter the basic information of subjects according to the system prompts, including the date of birth and

the name abbreviation, etc. The system will generate a unique random number for each subject and randomly allocate subjects to the groups.

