### **3.3 Blinding and Unblinding**

The patients will be blinded. Due to the significant differences in appearance between the experimental and control devices, blinding the researchers will not be possible. Blinding of the patients will be broken until this trial is finished.

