## **4 Outcomes**

### **4.1 Primary outcome:**

The primary objective of this clinical trial will be to evaluate and validate the safety and efficacy of the telesurgery system in urologic surgery and compare it to local urologic surgery. The success was defined as the surgery being completed effectively as planned, without conversion to other surgical types and significant side injury or delays due to system malfunctions. Telesurgery was considered successful if it could be completed only using the telesurgery system without conversion to local surgery for any reason. The success or failure of each surgery will be jointly confirmed by the remote and local medical teams together.

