## **8.3 Efficacy analysis**

### **8.3.1 Primary outcome analysis**

The primary outcome will be analyzed by a non-inferiority analysis. According to the medical statistics scenario, the main efficacy evaluation is based on the intention-to-treat population set and per-protocol population set. The statistical description and inference will be based on the characteristics of the data, and the appropriate descriptive indicators and hypothesis testing methods will be selected.

The primary efficacy indicator of surgical success rate uses a non-inferiority test, with the following hypotheses tested:

Null hypothesis:  $H_0: PT - PC \leq -\Delta$ ;

Alternative hypothesis:  $H_1: PT - PC > -\Delta$ .

At  $\alpha = 0.025$  (one-sided test) and  $\beta = 0.2$  levels, the success rates of the two groups will be statistically described and compared, and the 95% confidence interval (CI) of the difference in success rates between the two groups will be calculated. If the lower limit of the 95% CI of the difference in success rates between the two groups is greater than the non-inferiority margin ( $-\Delta$ ), it can be concluded that the experimental group is non-inferior to the control group.

The difference in the primary outcome (success rate) between the telesurgery and local surgery groups will be compared using the Miettinen-Nurminen method or Newcombe-Wilson score method test, according to the success rate data. The tipping assay can be used to determine the robustness and sensitivity the statistical conclusion.

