### **8.3.2 Secondary outcomes analysis**

The differences in secondary outcomes will be compared as follows:

- (1) Categorical data: logistic regression (with Firth's correction) or Exact Fisher's test;
- (2) Continuous data: linear regression

The hospital or surgery type can be used as adjusting factors.

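### Randomisation is stratified by surgery type, but the SAP leaves that factor optional in the pooled secondary analyses; the block-size wording also contradicts itself

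*Combined protocol and SAP*

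**What the plan says.** - **Strata.** SAP 3.3 Randomization: "Stratification was identified by the surgery type (prostatectomy and partial nephrectomy) with the randomization conducted separately for each stratum". Centre is not a stratification factor.
- **Blocks.** Same section: "We used stratified randomization with random block sizes of four". No other size is named.
- **Protocol 3.2 Randomization** describes a central system ("The system will generate a unique random number for each subject and randomly allocate subjects to the groups") but mentions neither strata nor blocks.
- **Secondary outcomes.** SAP 8.3.2 gives logistic regression with Firth's correction or Fisher's exact test for categorical data and linear regression for continuous data. It then adds: "The hospital or surgery type can be used as adjusting factors".
- **Primary outcome.** Under SAP 8.3.1 the success rates "will be compared using the Miettinen-Nurminen method or Newcombe-Wilson score method test, according to the success rate data". Surgery type and a stratified form are not mentioned.
- **Blinding.** Protocol 3.3: "blinding the researchers will not be possible". On who decides success, SAP 4.1 says: "The success or failure of each surgery will be jointly confirmed by the remote and local medical teams together".

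**The concern.** A factor used to restrict randomisation should normally appear in the analysis. When the arms are balanced on surgery type by design and the model omits it, the variation between the two operations stays in the residual. Standard errors for outcomes that depend on the operation are then too wide. The SAP permits adjustment without requiring it, and joins hospital and surgery type with an or. The analyst could therefore choose the model after seeing the results. Many secondary outcomes pool both operations: blood loss, operative time, stay, critical-care days, complications, QoR-15, the chair-stand test and team task load.

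The block wording is a separate matter. Random block sizes need at least two sizes and only four is given, so the sentence cannot be right as written. The natural reading is a constant block of four. Staff who know completed allocations could then sometimes foresee the next one. SAP 8.2.2 lists measures of surgical difficulty (BMI, R.E.N.A.L. score, prostate volume, Gleason score) on which cases could in principle be selected.

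**Working it through.** **Inputs from the documents.** 34 per arm, 68 in total; expected success 98% in both arms; margin 10 points; one-sided 0.025; each procedure at least 30% of cases (all SAP 3.2). Two strata and a block size of four (SAP 3.3).

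**Assumptions.** The share of variance explained by surgery type, the split between strata, and the stratum-specific success rates. The documents give none of these.

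**1. The plan's own sample size.** n = (1.960 + 0.842)² × [0.98 × 0.02 + 0.98 × 0.02] / 0.10² = 7.849 × 0.0392 / 0.01 = 30.77, so 31 per arm. This reproduces the stated figure. The formula has no term for surgery type.

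**2. Secondary outcomes.** If surgery type explains a share R² of the variance, the model that includes it has residual variance (1 − R²) times the total. An unadjusted analysis of N patients then has the precision of an adjusted analysis of N(1 − R²).

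| Assumed R² | 68 × (1 − R²) |
|---|---|
| 10% | 61.2 |
| 30% | 47.6 |
| 40% | 40.8 |

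The price of adjusting is one residual degree of freedom (68 − 2 = 66 becomes 68 − 3 = 65).

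**3. Primary outcome.** Crude Miettinen-Nurminen was compared with a version stratified by surgery type, weights n₁n₀/(n₁ + n₀), by enumerating binomial outcomes. Non-inferiority is declared when z > 1.96.

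| Per arm (split) | Power at 98%/98%, crude | Power at 98%/98%, stratified |
|---|---|---|
| 34 (17/17) | 0.302 | 0.271 |
| 34 (24/10) | 0.302 | 0.282 |
| 31 (16/15) | 0.257 | 0.257 |

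The 24/10 split is close to the 30% floor (10/34 = 29%).

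Type I error was checked in one null case: control success 99% and 95% in the two strata, telesurgery 10 points lower in each. At 34 per arm it was 0.020 crude against 0.014 stratified (17/17), and 0.017 against 0.014 (24/10). All are below 0.025.

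The choice can change the conclusion. With 34 per arm, 1 telesurgery failure and 2 local failures, the crude lower limit is −9.92% (z = 1.969), which passes. Stratified 17/17, the result depends on where the local failures fall:
- both in the stratum of the telesurgery failure: z = 1.941, fails;
- one in each stratum: z = 1.950, fails;
- both in the other stratum: z = 2.009, passes.

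**4. Blocks of four.** There are six orders of AABB. In AABB and BBAA the last two places are determined by the first two. In the other four orders only the last place is determined. That gives 2 × 2 + 4 × 1 = 8 of 24 places, or 33.3%. The best guess is right with probability 1/2, 2/3, 2/3 and 1 at the four places, a mean of 70.8% against 50% by chance.

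**The case against.** The strongest reply is that nothing here invalidates the primary analysis, and that stands. A reader might infer that leaving out the strata makes the primary test unsafe. The documents and the check do not support this: type I error stayed below 0.025 in the cases run, and SAP 8.3.1 is silent about strata rather than against them. A reader might also infer that stratifying the primary interval is a costless repair. At the planned 34 per arm it is not: power falls by 2 to 3 points, and a crude pass can become a fail.

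On blocks, a reader might infer that a third of allocations were foreseeable in practice. That requires someone who knows the block size and sees every earlier allocation in the stratum. Independent statisticians prepare the list, a central system holds it, and each stratum runs across several centres, so one site sees only part of the sequence. Nor is the absence of block size from protocol 3.2 a fault, since it helps concealment. Only the missing stratification factor needs adding there.

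It is also fair to say that the documents give no data on how far the two operations differ. The reason they offer for choosing both is to represent upper and lower urinary tract surgery. The variance shares above are therefore assumptions, shown as a range. Some outcomes come from one procedure only, and surgery type has no place in those analyses.

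None of this answers the optional wording in SAP 8.3.2 or the contradictory block sentence.

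**Conclusion.** The point holds for the pooled secondary outcomes. The stratification factor should be a fixed covariate, and the SAP only permits it. The loss is equivalent to about 7 to 27 of 68 patients (68 − 61 to 68 − 41) if surgery type explains 10% to 40% of the variance, and the choice of model is left open until after the data are seen.

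For the primary outcome the defect is incomplete pre-specification. Whether to stratify is a trade-off, and the power figures depend on the assumed splits and on n, since crude and stratified power agree at 31 per arm. That all of these powers lie far below the planned 80% is a separate sample-size question, which stratification neither causes nor cures.

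The block sentence is self-contradictory. If the size is fixed at four, one third is the most that could be determined, and actual predictability at any one site should be lower.

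**What to change.** - **SAP 8.3.2.** Replace the optional wording: surgery type is a covariate in every secondary model to which both procedures contribute. Exempt warm ischaemia time, EPIC-26, Gleason score and lymph node count. State in advance whether hospital is also included. Fisher's exact test takes no covariate, so say when it replaces the Firth regression.
- **SAP 8.3.1.** Name one unstratified score interval as primary. Add the Miettinen-Nurminen interval stratified by surgery type as a sensitivity analysis, and report the difference by surgery type.
- **SAP 3.3.** Correct the block sentence to what was actually done. If any of the list is unused, generate the remainder with block sizes varied at random, and keep the sizes out of documents that sites hold.
- **Protocol 3.2.** State the stratification factor, without block sizes.

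The cost is wording, plus regenerating any unused part of the list. The secondary change is a free improvement and needs no more patients. Varied blocks can leave the arms unequal by one or two patients. Keeping the unstratified interval as primary avoids the power cost.

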## **4 Outcomes**

### **4.1 Primary outcome:**

The primary objective of this clinical trial will be to evaluate and validate the safety and efficacy of the telesurgery system in urologic surgery and compare it to local urologic surgery. The success was defined as the surgery being completed effectively as planned, without conversion to other surgical types and significant side injury or delays due to system malfunctions. Telesurgery was considered successful if it could be completed only using the telesurgery system without conversion to local surgery for any reason. The success or failure of each surgery will be jointly confirmed by the remote and local medical teams together.

### **4.2 Secondary outcomes:**

The secondary outcomes of this study will be to investigate differences

between telesurgery and local surgery in terms of complications and early recovery quality, physical functioning, early oncological outcomes, task load of the surgeon and medical team, adverse events, and status or malfunction of the local surgery robotic or telesurgery system.

#### **4.2.1 Early recovery**

The following tools will be used to measure the early recovery:

1. Overall functional recovery: Quality of recovery 15-item score (QoR-15 score) at baseline (preoperative), 4 weeks, and 6 weeks.
2. Overall functional recovery for prostate cancer patients: Expanded Prostate Cancer Index Composite-26 (EPIC-26 score) at baseline (preoperative), 4 weeks, and 6 weeks.
3. Physical activity: 30-second chair-to-stand test (number of times the patient can stand from sitting in a 30-second interval) at baseline (preoperative), 4 weeks, and 6 weeks.

#### **4.2.2 Perioperative morbidity**

To assess perioperative morbidity, the following clinical data will be collected:

1. Surgery-associated factors: intraoperative blood loss, operative time, and warm ischemia time (for partial nephrectomy).
2. Complications and adverse events: Adverse events will be recorded

using the Clavien-Dindo classification at 4 weeks and 6 weeks postoperatively.

3. Postoperative hospitalization days.
4. Length of days in critical care.
5. Reoperational intervention.
6. Readmission to the hospital: Readmission to the hospital for any reason will be recorded, and the surgery-associated condition will be systemically reviewed.
7. Intra- and postoperative blood transfusion rates.
8. Mortality rate.

#### **4.2.3 Oncological outcomes**

To assess the oncological outcomes, the following pathological data will be collected:

1. Positive margin rate in the pathological specimen according to the pathology report from two blinded pathologists in each hospital.
2. Pathological type of the tumor;
3. The Gleason score and number of retrieved lymph nodes in the pathological specimen for prostatectomy with lymph node dissection only.

#### **4.2.4 Task load of medical team**

The NASA (National Aeronautics and Space Administration) Task Load Index (NASA-TLX) will be used to measure the task load of the first surgeon, first assistant, and instrument nurse immediately after the surgery in both groups.

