### **3.4 Study Treatment**

#### **3.4.1 Surgeon and unit accreditation**

The surgeon's experience and habits can impact various aspects of surgical performance, such as safety, operative time, and outcomes. For this trial, surgeons should complete more than 500 robot-assisted laparoscopic surgery procedures, including prostatectomy and partial nephrectomy. The surgical approach will be determined according to the protocol of the trial hospital where the patient is situated to facilitate the generalizability of the findings.

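### SAP 8.3.2 treats repeated NASA-TLX ratings by the same staff as independent; if operators differ by arm, standard errors are too small

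*Combined protocol and SAP*

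**What the plan says.** NASA-TLX is to "measure the task load of the first surgeon, first assistant, and instrument nurse immediately after the surgery in both groups" (SAP 4.2.4; Protocol 2.2.4 is the same). At 34 operations per arm that is 68 ratings per role, or 3 × 68 = 204 in all.

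For analysis, SAP 8.3.2 gives one line: "2) Continuous data: linear regression". It allows hospital or surgery type as covariates but does not require either. No section mentions a surgeon or rater effect, a mixed model or clustered standard errors, or says whether the three roles are analysed separately or pooled.

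Protocol 3.4.1 recognises the source of the correlation: "The surgeon's experience and habits can impact various aspects of surgical performance, such as safety, operative time, and outcomes". Its response is an experience threshold of more than 500 robotic procedures and, in 3.4.3, accreditation and a standard technique. These are design measures; nothing corresponds to them in the analysis. Randomisation is stratified by surgery type only (SAP 3.3).

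**The concern.** Two ratings by the same person share that person's way of using the scale. Two operations by the same surgeon share that surgeon's speed and habits. Ordinary linear regression counts each as a separate piece of information.

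What this does to a comparison of arms depends on who works where. If telesurgery and local operations are done by different people, differences between individuals enter the arm difference and the model does not see them. A few surgeons' scoring habits could then be reported as an effect of telesurgery on workload. If the same people work equally in both arms, their habits cancel from the difference, and the model leaves them in the residual as avoidable noise.

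Task load is a named comparison between arms, so a reader will want to know which case applies. The documents do not say.

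**Working it through.** **The plan's own figure.** The only sample size stated is for the primary outcome. With success rates of 98% in both arms, a 10-point margin, one-sided 0.025 and 80% power: n = (1.960 + 0.842)² × 2 × 0.98 × 0.02 / 0.10² = 30.77, so 31 per arm, as stated. Allowing for 10% dropout, 31/0.9 = 34.4; the plan enrols 34. I use 34 per arm below. There is no power, correlation or interval for task load to reproduce.

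**Assumptions, not in the documents.** K = 3 or 5 operators per arm for a given role, so m = 34/3 = 11.3 or 34/5 = 6.8 operations each; intraclass correlation (ICC) by operator 0.05 to 0.30; total variance 1.

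**Formulas for the true variance of the arm difference**

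- Independent ratings: 2/34, SE = 0.243.
- Different operators in each arm: (2/34) × [1 + (m − 1) × ICC].
  - m = 6.8, ICC 0.05: 1 + 5.8 × 0.05 = 1.29; SE ratio √1.29 = 1.14.
  - m = 11.3, ICC 0.30: 1 + 10.3 × 0.30 = 4.10 (unrounded m); SE ratio √4.10 = 2.02.
- One remote surgeon for all telesurgery, K local surgeons: ICC + ICC/K + 2(1 − ICC)/34.
  - K = 3, ICC 0.30: 0.300 + 0.100 + 0.041 = 0.441; SE = 0.664.
- Same operators balanced over both arms: (2/34) × (1 − ICC). Ordinary regression overstates this variance by about 1/(1 − ICC): 1.05 at ICC 0.05, 1.43 at 0.30.

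**Simulated coverage of the nominal 95% interval from ordinary linear regression** (5,000 runs per row; Monte Carlo error at most 0.7 points). Hospital is modelled as one operator per hospital in each arm.

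| Arrangement | Operators | ICC | SE, formula | SE, simulated | Coverage, arm only | Coverage, hospital added |
|---|---|---|---|---|---|---|
| Different people by arm | 5 per arm | 0.05 | 0.276 | 0.279 | 91.3% | 90.6% |
| Different people by arm | 5 per arm | 0.30 | 0.401 | 0.403 | 75.3% | 73.4% |
| Different people by arm | 3 per arm | 0.05 | 0.299 | 0.298 | 89.0% | 88.1% |
| Different people by arm | 3 per arm | 0.30 | 0.491 | 0.494 | 64.1% | 61.8% |
| One remote surgeon | 5 local | 0.05 | 0.340 | 0.344 | 83.1% | 83.7% |
| One remote surgeon | 3 local | 0.30 | 0.664 | 0.664 | 47.4% | 46.7% |
| Same people, balanced | 3 | 0.05 | 0.236 | 0.239 | 94.9% | 94.6% |
| Same people, balanced | 5 | 0.30 | 0.203 | 0.203 | 97.6% | 94.8% |

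Formula and simulation agree. With different people by arm, a nominal 5% test errs about 9% to 36% of the time (100% minus coverage). With the same people in both arms, the hospital term in this model is also the operator term. It returns coverage to 95% and, at ICC 0.30, shortens the mean interval from 0.92 to 0.81 (3 operators) or 0.94 to 0.81 (5 operators).

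**The case against.** The best defence is that patients are individually randomised, so a shared operator does no harm by itself. If the same staff serve both arms in balance, the planned regression is valid or mildly conservative, and the optional hospital covariate recovers much of the lost precision. That stands. A reader might infer that the intervals are wrong whichever way staff are allocated; the 95% to 98% coverage in the balanced case does not support that.

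Nor do the documents show that only a few people are involved. No count is given for any role, and the experience and accreditation rules apply to surgeons only. Repeated rating is an inference from 68 operations and about five sites. It is a strong one, but how many ratings come from each person is unknown.

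The damaging case is also not equally likely for all roles. The patient cart stands in the patient's hospital, so assistants and nurses are probably local staff working in both arms, though this is not stated. For the first surgeon, Protocol 3.4.2 puts the main console in that surgeon's own hospital or laboratory, with another surgeon at the patient's side. Nothing requires the same person to operate in both arms.

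Finally, SAP 8.3.1 specifies a 95% interval for the primary outcome only, the SAP calls the trial exploratory, and task load is one of many secondary outcomes. This limits the consequence, but the same standard errors drive any p-value or interval reported for task load.

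**Conclusion.** The gap is real: repeated ratings by one person are close to certain, and SAP 8.3.2 makes no provision for them. Its size and direction cannot be fixed from the documents.

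Under the assumed 3 to 5 operators per arm and ICC of 0.05 to 0.30, coverage is 91% down to 64% if operators differ by arm, and 83% down to 47% if one remote surgeon does all the telesurgery. Hospital adjustment helps in neither case. If the same people work in both arms in balance, there is no excess of false findings, only lost precision.

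A reader might extend the coverage figures to operative time, blood loss and warm ischaemia time. These are measured on patients rather than rated by staff, and the documents give no basis for assuming the same ICC. They justify a sensitivity analysis, not the same claim. Nothing here changes the sample size or the planned primary analysis. The change is worth making because it is cheap and suits either allocation of staff.

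**What to change.** In SAP 8.3.2, before the data are analysed:

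- Record an operator ID for each of the three roles at every operation. The table of assessments (Protocol 5) shows no such field.
- Analyse NASA-TLX separately by role, with arm and surgery type as fixed effects and a rater effect. Use a random intercept with small-sample degrees of freedom (Kenward-Roger), or a fixed rater effect where raters are few and work in both arms.
- Report the number of operators by role and arm, and how many work in both.
- If no first surgeon works in both arms, state that arm and surgeon cannot be separated and present first-surgeon task load descriptively. No model solves this. Even with 3 surgeons per arm, the comparison would rest on about 2 × 3 − 2 = 4 degrees of freedom.
- For operative time, blood loss and warm ischaemia time, add a first-surgeon effect as a sensitivity analysis.

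The cost is one more recorded field per role, a few lines of SAP text, and wider intervals if operators are not shared between arms.
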